The second aim is to examine potential moderators of the effect of R&W. Several student characteristics will be examined as moderators: Gender, ethnicity, and personality. In the R&W program the emphasis is on physical exercises which might lead to differential effectiveness based on gender and ethnicity. There are differences in the levels of daily physical activity between boys and girls with girls being less physically active [12, 13]. Girls appear to experience higher barriers for physical activities than boys. They are more afraid of being chosen last for a team and of being embarrassed [13]. Therefore, we hypothesize that R&W is more effective for boys.

Also between ethnicities there are differences in the amount and sort of physical activities adolescents engage in. For instance, Black and Asian adolescents are less physically active and show more sedentary behavior than White adolescents [12, 14]. White girls are more likely to be active in sports teams than Hispanic girls whom are more likely to be active in walking for transportation or physical activities at home such as household chores [15]. Kelly and colleagues [15] suggest to tailor physical activity programs based on ethnicity due to differences in factors related to physical activation. For example, White girls appear to have higher levels of self-efficacy related to physical activities which makes them more physically active than Black and Hispanic girls. It might be that White students are more familiar with the sort of physical exercises used in the R&W program than students with other ethnicities. These White students might be less out of their comfort zone due to which they can focus more on the other aspects of the intervention. Thus, we hypothesize that R&W is more effective for White students than for students with other ethnicities.

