## Methods

### Design

To study the effects of R&W an RCT design is implemented in the 7th Grade of preparatory vocational education level. Schools from different parts of The Netherlands are randomly assigned to one of three intervention groups or to the control group (Fig. 1). In the ‘Light’ condition a core team of teachers is trained with the three-day training course to become certified R&W trainers and implement the R&W program. In the ‘Standard’ condition a core team is trained to become R&W trainers and the rest of the school-team that teaches 7th Grade students follows a three-day training to learn how they can support the R&W trainers of their school and how they can apply R&W in their regular classes. The ‘Plus’ condition is equal to the ‘Standard’ condition with the addition of a parent component. The parents watch a documentary of R&W, get an invitation to join a lesson in the school, receive weekly e-mails with information about the lesson of that week and are stimulated to act on this information, for instance by communicating about R&W or using R&W language. This will not only create a supporting environment within the school, but also in students’ homes. In the control condition students receive CAU; i.e., current school policy to enhance socio-emotional adjustment and social safety of students.

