### Recruitment

Schools were recruited through the network of the developers of R&W, the Gadaku Institute. An e-mail to certified R&W trainers was sent with information about this study and a message on the private R&W online forum was posted. Trainers asked within their network whether schools that did not implement R&W were interested in participating in this study. When schools were interested they contacted the Gadaku Institute which referred the school to the researchers. The researchers established whether the school was eligible for participation. If the school was eligible, the researcher provided additional information to the schools based on which the school made a decision concerning participation.

Schools were randomly assigned (1:1:1:1 ratio) by stratified block randomization, with blocks of four (i.e., the number of conditions in this study). Schools were stratified by school size (small to moderate sized schools: < 100 students in 7th Grade, large sized schools: > 100 students in 7th Grade) to establish a more equal distribution of students over the four conditions. The randomization numbers were generated by a random number generating computer program.

Students, parents, teachers, and R&W trainers received an information letter to inform them about R&W and the study. Parents also attended a parent-teacher evening where they received additional information about R&W. Students gave active informed consent and parents passive informed consent for participation of the student. Parents gave active informed consent for their own participation in the study. Active informed consent was also acquired for participation of teachers and R&W trainers.

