#### Moderators

Students’ gender and ethnicity and trainers’ gender, ethnicity, education, expertise, and degree of received training and supervision are assessed with questionnaires developed for this study.

Students’ personality is reported by the student and parent using the Quick Big Five [41]. It consists of 30 items (i.e., characteristics; e.g., nice, sympathetic, organized) on which the informant can indicate to what extent that characteristic suites the participant.

Parental sense of parenting competence is assessed with the subscale Competence of the Parenting Stress Index [42] completed by the parent. It measures the degree to which parents feel they are capable enough and have enough skills to cope with their child. The subscale contains 8 items (e.g., “Raising my child is harder than I expected.”).

Positive parenting will be measured using the subscales Warmth and Monitoring from the Co-parenting Behavior Questionnaire [43] completed by the parent. The subscale Warmth (7 items; e.g., “I spend time doing fun things with my child.”). measures the extent to which parents show parenting behavior to make their children feel comfortable, accepted and approved. The subscale Monitoring (5 items; e.g., “I know my child’s after school activities.”) measures parental awareness of different aspects of the children’s life.

Teacher’s sense of competence will be assessed with the subscale Self-efficacy for management of the Teachers’ sense of self-efficacy [44] completed by the R&W trainer. This subscale measures teachers’ confidence in their skills to effectively manage their classroom. It contains 6 items (e.g., “How much can you do to control disruptive behavior in the classroom?”).

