#### Statistical analyses

The power calculations are based on the N:q rule for structural equation models [59]. This rule states that for each free parameter (q) 10 to 20 participants (N) are needed. We took the conservative approach by taking 20 participants per free parameter for our power calculations. In our multigroup LGC model there are 9 free parameters per condition, 36 free parameters in total. Thus a total sample of 720 participants is needed for our analysis, 180 participants in each condition. Since not only students can drop out but also classes (about 20 students) and schools (about 60 to 90 students), we will include three to four schools per condition. Missing data will be handled in M*plus*.

In our data, students are nested in classes which are nested in schools. Therefore, we will examine whether there is significant intra-class correlation on one of the levels (i.e., school, and class) and we will calculate the design effect. Each level with a design effect larger than 2.0 will be modeled in the analyses which allows us to correct for the nested data, that is multilevel analyses [60].

The first aim is to examine the effectiveness of R&W in the conditions which differ in the number of parties involved in the intervention. This will be examined using an analysis of covariance (ANCOVA) for the outcomes of socio-emotional adjustment and social safety, in case the design effect is smaller than 2.0. The dependent variables will be the post-measurements after the second year (8th Grade), the independent variables the condition, and the covariates the premeasurements (7th Grade). If needed, due to large design effects, multilevel regression analyses will be used (This also holds for the other aims). Then, we will analyze the trajectories of change in socio-emotional adjustment and social safety during R&W with multigroup Latent Growth Curve (LGC) modeling in M*plus*. We will examine if these trajectories of change differ significantly between the four conditions.

The second aim, the effect of potential moderators on the effectiveness of R&W on socio-emotional adjustment and social safety, will be examined using ANCOVAs for categorical moderators and regression analyses for the continuous moderators. The interaction effects of the concerned outcome measure with the student, trainer or parent characteristics will be added as an interaction term.

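### The aim-1 model is valid with the pre-measurement alone, but leaves out student gender and ethnicity, which are already collected and could give a modest gain in precision with only 12 to 16 schools

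*Protocol article*

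**What the plan says.** - **Model.** The Statistical analyses section gives the aim-1 dependent variable as the measurement after the second year, with "the independent variables the condition, and the covariates the premeasurements (7th Grade"). No other covariate is named.
- **Clustering.** ANCOVA applies when the design effect is below 2.0. Otherwise: "If needed, due to large design effects, multilevel regression analyses will be used (This also holds for the other aims").
- **Allocation.** Under Design, "Schools from different parts of The Netherlands are randomly assigned to one of three intervention groups or to the control group". Under Recruitment, "Schools were randomly assigned (1:1:1:1 ratio) by stratified block randomization, with blocks of four", and "Schools were stratified by school size". No other stratification factor is given.
- **Number of schools.** "we will include three to four schools per condition".
- **Available covariates.** Under Moderators, "Students’ gender and ethnicity" are assessed by questionnaire. The analysis section uses student characteristics only as aim-2 interaction terms.
- **Hypothesis.** In the Background, for the second aim: "we hypothesize that R&W is more effective for White students than for students with other ethnicities". A greater benefit for boys is also expected.

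**The concern.** With so few schools, drawn from different regions and stratified by size alone, randomisation cannot be relied on to give the four conditions a similar ethnic or gender mix. If either characteristic predicts the two-year outcome after the pre-score is taken into account, a chance difference in mix enters the one estimate that the trial will produce. That affects each comparison with control and the comparison of Light, Standard and Plus. Both characteristics precede allocation and are already measured, so leaving them out gives up some precision. It also leaves open a decision to adjust after the mix has been seen.

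**Working it through.** **1. The plan's own figures.** The N:q rule gives 20 × 9 × 4 = 720, and 720 / 4 = 180 per condition, as stated. Schools: 3 × 4 = 12 to 4 × 4 = 16. At 180 per condition this is m = 60 students per school (k = 3) or m = 45 (k = 4).

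**2. Assumptions (none is in the documents).** Minority share p = 0.3 with between-school SD s = 0.10 to 0.25. Gender share p = 0.5 with s = 0.03 to 0.08. Gender and ethnicity effects b = 0.1 to 0.3 SD. Pre-post correlation r = 0.6. School ICC 0.01 to 0.05.

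**3. Chance difference in mix between two conditions.** Variance of the difference in share = 2 × (s² + p(1 − p)/m) / k.
- Ethnicity, k = 3, s = 0.25: 2 × (0.0625 + 0.0035) / 3 = 0.0440, SD 21 points.
- Ethnicity, k = 4, s = 0.10: 2 × (0.0100 + 0.00467) / 4 = 0.00733, SD 9 points.
- Gender, k = 3, s = 0.08: 2 × (0.0064 + 0.00417) / 3 = 0.00704, SD 8 points.
- Gender, k = 4, s = 0.03: 2 × (0.0009 + 0.00556) / 4 = 0.00323, SD 6 points.

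**4. What a 1-SD imbalance does.** Without the pre-score the shift is b × SD, from 0.1 × 0.057 = 0.006 to 0.3 × 0.210 = 0.063 SD. If the characteristic acts equally on pre- and post-score, adjustment leaves (1 − r) = 0.4 of that: 0.002 to 0.025 SD. If b is instead an effect beyond the pre-score, the whole shift remains.

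**5. Variance that the covariates could remove.** Without mix, the variance of a difference is V0 = (2/180) × (1 − 0.36) × [1 + (m − 1) × ICC]. Mix adds Vm = b² × (ethnicity variance + gender variance). The removable share is Vm / (V0 + Vm), with b taken as the effect beyond the pre-score.
- Wide mix, k = 3: Vm = b² × 0.0510. V0 = 0.0113 at ICC 0.01 and 0.0281 at ICC 0.05.
- Narrow mix, k = 4: Vm = b² × 0.0106. V0 = 0.0102 at ICC 0.01 and 0.0228 at ICC 0.05.

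| b beyond pre-score | Wide mix, ICC 0.01 | Wide mix, ICC 0.05 | Narrow mix, ICC 0.01 | Narrow mix, ICC 0.05 |
|---|---|---|---|---|
| 0.1 | 4% | 2% | 1% | 0.5% |
| 0.2 | 15% | 7% | 4% | 2% |
| 0.3 | 29% | 14% | 9% | 4% |

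These are ceilings, because they ignore the cost of estimating two coefficients.

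**6. Simulation.**
- Effects beyond the pre-score, ICC 0.01 to 0.03: one set of runs gave cuts of almost nothing (0.1 SD), 2% to 12% (0.2 SD) and 5% to 22% (0.3 SD). Other settings reached 28%, and 33% with an ethnic-share SD of 0.30.
- Effects equal on pre and post, r = 0.6, ICC 0.02 to 0.05: the SD of the estimated difference changed by −1.7% to +0.6%. With no true effect, the mean estimate stayed within 0.01 SD of zero with and without the covariates.

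**7. Growth model.** Assume two growth factors and one term per covariate. Predicting both factors adds 4 parameters per condition: 36 + 16 = 52, and 52 × 20 = 1,040 students. With slopes held equal across conditions it is 36 + 4 = 40, and 40 × 20 = 800. Both exceed 720.

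**The case against.** ANCOVA on the pre-measurement of the same outcome is a sound analysis of a randomised trial. A reader might infer that imbalance in mix biases the aim-1 result, or that all of it stays in the effect. The documents support neither. Randomisation makes the error zero on average, and the pre-score takes out imbalance already visible at baseline. Where the characteristics act equally on both scores, what is left (0.002 to 0.025 SD for a 1-SD imbalance) is small beside a standard error of about 0.12 to 0.17 SD at ICC 0.02 to 0.05. This stands.

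A reader might also take the Background hypotheses as evidence that gender and ethnicity are prognostic. They concern effect modification, which aim 2 tests. They do not say that either variable predicts the outcome beyond the pre-score, and main-effect covariates would not remove a difference that arises from moderation. This stands too, so the size of the gain rests on assumption.

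The remaining error is reflected in the standard error only if the school level is modelled. At 45 students per school and ICC 0.02 the design effect is 1 + 44 × 0.02 = 1.88, so the plan would use single-level ANCOVA, with a standard error of 0.084 instead of 0.116 SD. That is a matter of the design-effect rule. The covariates would not cure it.

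Further covariates might also stand in a fuller plan that is not shown. Against that, the article does state its covariates, and the suggestion addresses that statement.

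**Conclusion.** This is an optional improvement in precision, of minor weight. It is neither an error nor a contradiction. The facts hold: one covariate is named, two further pre-randomisation student variables are collected, and 12 to 16 schools are stratified by size only. The gain runs from nothing (effects of 0.1 SD, or effects carried by the pre-score) to roughly 5% to 28% of the variance of a between-condition difference (effects of 0.2 to 0.3 SD beyond the pre-score, low school ICC). In standard-error terms 5% to 28% is about 3% to 15%, since 1 − √0.95 = 0.025 and 1 − √0.72 = 0.15. The upper end needs a wide ethnic mix between schools and strong effects of both variables. The gain shrinks as the ICC rises, and the worst simulated result was a variance loss of about 2%. All of this rests on assumed mix, effects, correlation and ICC.

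**What to change.** Pre-specify student gender and ethnicity as fixed student-level covariates next to the pre-measurement in the aim-1 ANCOVAs or multilevel regressions, and in the aim-3 ANCOVAs of the mediators. Settle this before outcomes are seen, with the ethnicity categories and the handling of missing values, since the article states neither the categories nor how complete the data will be.

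The cost is a few student-level degrees of freedom and those two decisions. No new data are needed, and as student-level terms they use no school-level degrees of freedom. Do not require the covariates in the multigroup growth model: they add free parameters beyond the 36 that underlie N = 720 at the protocol's chosen ratio of 20.

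### If school is modelled, three to four schools per condition cannot reliably support condition-specific school-level growth parameters, and large-sample tests would reject too often

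*Protocol article*

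**What the plan says.** All of this is in the protocol article.

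- **Randomisation** (Recruitment): "Schools were randomly assigned (1:1:1:1 ratio) by stratified block randomization, with blocks of four". The school is the randomised unit, so each school sits in one condition only.
- **Number of schools** (Statistical analyses): "we will include three to four schools per condition". The reason given is possible drop-out of students, classes and whole schools, with sizes stated as "classes (about 20 students) and schools (about 60 to 90 students".
- **Growth model and sample size** (Statistical analyses): "In our multigroup LGC model there are 9 free parameters per condition, 36 free parameters in total". Then "We took the conservative approach by taking 20 participants per free parameter for our power calculations", and "Thus a total sample of 720 participants is needed for our analysis, 180 participants in each condition".
- **Test of trajectories** (Statistical analyses): "We will examine if these trajectories of change differ significantly between the four conditions".
- **Clustering rule** (Statistical analyses): class and school are each checked, and a level whose design effect exceeds 2.0 enters the model. For the aim-1 ANCOVA, and for the other aims, the section says "If needed, due to large design effects, multilevel regression analyses will be used (This also holds for the other aims".

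The article does not say whether school-level variances would be specific to each condition or common to all. It names no estimator or reference distribution for the multilevel tests, and no alpha.

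**The concern.** Three choices that the article fixes fit badly together: a growth model whose counted parameters are all condition-specific, a rule that brings the school level into the model at a low intra-class correlation, and 12 to 16 schools in total.

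If the multigroup form is carried to the school level, each condition's school-level growth parameters rest on three or four schools. Whole schools are expected to be able to leave, so this could become fewer. Separately, any test of condition in a model with a school level has few degrees of freedom, and tests that treat the number of schools as large reject too often.

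At stake are the trajectory comparison and the main comparison of conditions, in exactly the situation where clustering matters. The 720 students do not help, because the information on condition lies between schools.

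**Working it through.** **Inputs from the article:** 9 free parameters per condition, 4 conditions, 20 participants per parameter, 3 to 4 schools per condition, 60 to 90 students per school, 20 per class, design-effect limit 2.0.

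**Assumptions, not in the article:** two-sided alpha 0.05, linear growth, balanced schools, equal school variance across conditions, no school-level covariate.

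**1. The plan's own figure.** 9 × 4 = 36 parameters; 36 × 20 = 720; 720 / 4 = 180. Reproduced. The rule counts students; the number of schools is not checked against a multilevel model.

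**2. When school enters the model.** Design effect = 1 + (m − 1) × ICC, which exceeds 2.0 when ICC > 1/(m − 1).
- School of 60: 1/59 = 0.017. School of 90: 1/89 = 0.011.
- Class of 20: 1/19 = 0.053.

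A small school ICC is therefore enough.

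**3. School-level parameters against schools** (12 to 16 in total).
- Growth model, school level specific to each condition: 2 means + 2 variances + 1 covariance = 5 per condition; 4 × 5 = 20.
- Growth model, school (co)variances common to all conditions: 8 means + 3 = 11.
- Multilevel regression: 4 condition means + 1 covariate + 2 variances = 7 parameters in all, or 8 with a class level.

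With three schools in a condition, three intercept-slope pairs supply two means and a 2 × 2 covariance matrix on 2 degrees of freedom. That is just enough for five parameters, with very poor precision. With two schools there is 1 degree of freedom, and an unrestricted 2 × 2 covariance matrix can no longer be estimated.

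**4. True error of a nominal 5% single contrast tested against 1.96,** when between-school variance dominates. With J schools, df = J − 4.
- REML: 2 × P(t_df > 1.96)
- ML: 2 × P(t_df > 1.96 × √(df/J)), because ML divides by J instead of df

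| Schools | df | REML, z test | ML, z test | Critical t |
|---|---|---|---|---|
| 12 | 8 | 8.6% | 14.8% | 2.31 |
| 16 | 12 | 7.4% | 11.5% | 2.18 |

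For the joint 3-df comparison of the four conditions, a chi-square Wald test has true error 12.4% (REML) or 23.7% (ML) with 12 schools, and 10.0% or 17.5% with 16. The ML likelihood-ratio test gives 13.9% and 10.7%.

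**5. Simulation** (400,000 replicates per setting; 12 or 16 schools of 60 or 90; variance truncated at zero; single contrast, school always modelled).

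| School ICC | REML, z | ML, z | REML, t on 8 or 12 df |
|---|---|---|---|
| 0.05 to 0.20 | 7.3-8.6% | 11.4-14.9% | 4.9-5.0% |
| 0.01 to 0.02 | 6.4-8.2% | 8.9-13.4% | 3.4-4.9% |

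Among only those replicates whose estimated design effect passed 2.0, the z-test rates at ICC 0.05 are 6.0-7.2% (REML) and 10.1-13.2% (ML). At ICC 0.01 to 0.02 they are 1.5-4.4% and 3.7-9.1%. The inflation thus belongs mainly to outcomes with appreciable school variance. Replicates below the trigger would go to the analysis without a school level, which these figures do not cover.

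**The case against.** The strongest reply is that the article does not commit itself to the harmful version. The sentence on the fallback concerns multilevel regression, which with 7 or 8 parameters can be fitted on 12 to 16 schools and holds about 5% with a t reference. The count of 20 school-level growth parameters presumes that they are free in each condition, and the article does not exclude pooling. No estimator or reference distribution is stated for the multilevel tests. In a journal article, with the analysis plan not shown, the degrees-of-freedom method may properly be left to that plan.

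Most of this stands, and it rules out some tempting stronger readings:

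- A reader might infer that the multilevel fallback is unworkable. It is not: the regression is estimable, and its price is power and an imprecise school variance.
- A reader might infer that the school-level growth model is not identified. With three schools per condition it is just identified, only very imprecise; the breakdown comes at two.
- A reader might take the error rates as properties of the stated plan. They hold only if large-sample tests are used.
- A reader might expect the school level to be dropped after the data are seen. The rule on design effects says the opposite.
- An argument from the smallest p-value of an exact test of three against three schools bears on no planned analysis and ignores the stratified blocks of four.

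What the reply does not remove is the mismatch in what the article does fix. Its parameter count is wholly condition-specific, its rule brings in the school level at an ICC of 0.011 to 0.017, and its number of schools is justified by drop-out alone. Taken as written, the growth model goes to three or four schools per condition unless someone decides otherwise.

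**Conclusion.** The point holds in a limited form. If school is modelled and the multigroup form is kept at that level, about 20 school-level growth parameters rest on 12 to 16 schools, 5 of them on 3 or 4 schools within each condition. This is not reliably estimable and does not survive a condition falling to two schools.

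The multilevel regression is sound as a model. For either model, large-sample tests would put a nominal 5% single contrast at about 7-9% (REML) or 11-15% (ML) when between-school variance is appreciable, and lower near the design-effect trigger. The first conclusion assumes linear growth and school-level parameters left free in each condition; the second assumes uncorrected z or chi-square tests. The absence of a named degrees-of-freedom method is not in itself a fault of an article. The reason to act is that the structure the article fixes leads towards the fragile version, and the remedy is cheap.

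**What to change.** State that, when school is modelled, the trajectories are analysed in one growth (mixed) model over all four conditions. Condition indicators predict intercept and slope, and the school random intercept (with a random slope if it can be estimated) and class random effects are common to all conditions. With pooled (co)variances the school level has 11 parameters instead of 20.

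Estimate by REML and test condition effects with t or F on Kenward-Roger or Satterthwaite degrees of freedom, about 8 with 12 schools and 12 with 16. Use the same approach for the multilevel version of the aim-1 ANCOVA. In the simulation, REML with a t reference brought the single-contrast error to 3.4-5.0%.

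The cost is wording in the analysis section, an assumption that school-level variances are equal across conditions, and wider intervals (critical value 2.31 or 2.18 in place of 1.96). The article names M*plus* for the growth model; if that program does not offer these options, this part must be fitted in one that does.

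### The aim 2 interaction is written as outcome measure × characteristic and leaves out condition, so as worded it does not test moderation of the R&W effect

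*Protocol article*

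**What the plan says.** The Background sets the question: "The second aim is to examine potential moderators of the effect of R&W". Its hypotheses are all worded as differences in how well R&W works. For gender it says: "Therefore, we hypothesize that R&W is more effective for boys". It makes parallel statements for ethnicity, personality, trainer characteristics and parental characteristics. For conscientiousness the benefit is expected to be greatest at average levels.

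The Statistical analyses section restates the aim in the same terms ("The second aim, the effect of potential moderators on the effectiveness of R&W on socio-emotional adjustment and social safety") and says that it "will be examined using ANCOVAs for categorical moderators and regression analyses for the continuous moderators". It then defines the added term: "The interaction effects of the concerned outcome measure with the student, trainer or parent characteristics will be added as an interaction term".

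The same section has already assigned roles for aim 1. The post-measurement after the second year is the dependent variable, condition is the independent variable and the premeasurement is the covariate. It also says that multilevel regression, if large design effects call for it, applies to the other aims as well.

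**The concern.** Moderation of an intervention effect means that the difference between conditions changes with the characteristic. The model term that carries this is condition × characteristic. The plan's sentence pairs the characteristic with the outcome measure instead.

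Aim 2 is one of the trial's three aims and carries its claim to show what works for whom. If the sentence were followed to the letter, the reported coefficient would not bear on the hypotheses. It could miss real moderation, and it could also be significant when R&W works equally well in every subgroup. If the sentence is silently set aside, the published plan contains no correct statement of the test, although many moderators and outcomes are involved.

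**Working it through.** **1. The plan's own figure.** The section gives a sample size but no figure for the moderator analyses. From "In our multigroup LGC model there are 9 free parameters per condition, 36 free parameters in total" and "taking 20 participants per free parameter for our power calculations": 9 × 4 = 36 parameters, 36 × 20 = 720 students, 720 / 4 = 180 per condition. This reproduces exactly and does not depend on the aim 2 term.

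**2. What each reading of the sentence tests.** Let C be condition (R&W or control, for simplicity), M the characteristic and Pre the premeasurement.

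- *Outcome measure = post-score.* The model is Post = b0 + b1·C + b2·M + b3·Pre + b4·(Post × M) + e. A predictor is built from the dependent variable and is therefore tied to the error. This is not a valid model.
- *Outcome measure = premeasurement.* The model is Post = b0 + b1·C + b2·M + b3·Pre + b4·(Pre × M) + e. The effect of condition is b1 at every value of M, so the model assumes there is no moderation of R&W. The coefficient b4 says only whether the pre-post slope differs by M.
- *What the hypotheses need.* The model is Post = b0 + b1·C + b2·M + b3·Pre + b5·(C × M) + e. The effect of condition is b1 + b5·M, and moderation is b5 ≠ 0.

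**3. Illustrative simulation.** All effect sizes here are assumptions and none is in the article. The set-up was 720 students in four equal arms, a binary M coded ±0.5, baseline slope 0.5, R&W main effect 0.2, residual variance 0.75, no clustering, 4,000 replicates and a 5% level. The condition × M test has 3 degrees of freedom.

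| True condition × M | True Pre × M | Pre × M rejects | Condition × M rejects |
|---|---|---|---|
| 0 | 0 | 5.0% | 4.7% |
| 0.5 | 0 | 5.0% | 81% |
| 0 | 0.3 | 99.5% | 4.8% |

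**4. Range.** The power of the correct term depends heavily on the assumptions. For a binary M split evenly, Var(b5) = 4σ²(1/n₁ + 1/n₀). With an assumed interaction of 0.4 and σ² = 0.75:

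- 180 vs 180: Var = 3 × (2/180) = 0.0333, SE = 0.183, 0.4/SE = 2.19, power about 59%.
- 540 vs 180 (R&W arms pooled): Var = 3 × (1/540 + 1/180) = 0.0222, SE = 0.149, 0.4/SE = 2.68, power about 76%.

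In two-arm simulations of 360 students, raising the residual SD to 0.9 or 1.0 gave 55% or 47%. In those runs the Pre × M term stayed near 5%.

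**5. Where condition × characteristic needs adapting.**

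- *Trainer characteristics.* The Background and the Moderators section describe these for R&W trainers. The control arm receives care as usual and has no such trainers, so M has no control-arm values and C × M against control cannot be estimated.
- *Conscientiousness.* With a linear term, the condition effect b1 + b5·M only rises or only falls with M. A benefit that is greatest at average levels needs b1 + b5·M + b6·M², with b6 negative (scores coded so that higher is better) and the turning point −b5/(2·b6) near the average.

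**The case against.** The best defence is that this is a slip of the pen. The sentence before it defines the aim as moderation of R&W's effectiveness, the hypotheses are worded that way, and aim 1 makes condition the independent variable. A sympathetic reader would take the sentence to mean that, in the model for each outcome measure, an interaction with the characteristic is added to the aim 1 ANCOVA. That is probably what was meant, and it lowers the likelihood of harm. It does not rescue the wording, because the sentence names both parts of the interaction and condition is not one of them. Nor is this detail that an article leaves to a fuller plan: the term is stated, and stated wrongly.

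A reader might infer that every moderator hypothesis will be answered with the wrong coefficient. The article does not support that. It shows what is written, and its own aim points to a different intention. A reader might also take the simulated rates as the power this trial would lose. They are not. The 5% for the wrong term follows from its construction, and the rates for the correct term rest on assumed effects and ignore school and class clustering.

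It is also fair to object that a blanket condition × characteristic rule would not suit every moderator. That stands for trainer characteristics and conscientiousness. Using ANCOVA for categorical moderators and regression for continuous ones is no fault, since both are the same linear model.

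**Conclusion.** The point holds for the plan as written. The one sentence defining the aim 2 test names the wrong pair of variables, and on either literal reading the term does not measure moderation of the R&W effect. This follows from the algebra and needs no assumption about effect sizes.

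The practical size cannot be fixed from the article. Under the assumptions shown, the premeasurement reading stays near 5% when moderation exists and reaches 99.5% when only the pre-post slope differs. The correct term ranged from 47% to 81% when moderation was present. These figures are illustrative only.

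The error is confined to the stated test for aim 2. The aim 1 comparison, the randomisation, the data collected and the total of 720 are unaffected.

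**What to change.** Replace the sentence with wording along these lines:

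- *Student and parent characteristics.* The post-measurement is modelled on condition, the characteristic, condition × characteristic and the premeasurement, with clustering handled as for aim 1. The condition × characteristic term is the test of moderation.
- *Conscientiousness.* The squared term and its interaction with condition are added, because the hypothesis is a strongest effect at average levels.
- *Trainer characteristics.* These are examined within or among the three R&W arms and not against control. The report should say that such results describe how outcomes under R&W vary with the trainer, and not how the effect relative to care as usual varies.

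The cost is a short paragraph in the analysis section. No data, measurement or sample size changes. With four conditions, the conscientiousness model gains one squared term and three interaction terms. The first rule assumes that student and parent characteristics are collected in all four arms. The article's text does not restrict them to the R&W arms, and the instrument table in the supplement, which was not available here, should confirm it.
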